#### Data collection and data management

All subject data obtained during the study will be recorded using pseudonyms. Every patient will be clearly identified by a registration number and a pseudonym, which will be assigned during the registration process. The investigator keeps a confidential patient list, in which the patient number and pseudonym are connected to the complete patient’s name. Access to this list is only provided to the local study personal and the study monitor. The original source files and medical records directly related to the study can be accessed by study monitors, auditors or inspectors from regulatory authorities. All data collection of pseudonomized data will be done on standardized case report forms (CRFs), which will be completed by site staff, verified by the principal investigator, and returned to the clinical trials unit for double data entry. All data will be recorded electronically at the sponsor’s site by independent data managers. The sponsor will maintain a list of personnel authorized to enter data into the database. Validation of correct data entry will be ensured by the named data managers to check for discrepancies and to ensure consistency of the data. Validated data will be entered into an electronic trial database. Any addition, change or correction to the entered data must be approved by the investigator and will be recorded. Records of correction will be kept together with the case report form. Regular backups of the electronic data will be performed. When all data have been recorded and validated after termination of the study the database will be closed. This process will be recorded.

The sponsor maintains a list of personnel authorized to access the data.

#### Monitoring and auditing

The monitor has the responsibility to familiarize the investigator(s) and the entire center staff involved in the study with all study procedures including the administration of the study drug. The sponsor must provide a trained monitor to assist the investigator(s) in conducting the clinical study. The monitor must visit the clinical study center on a regular basis and at least once before the first subject has been enrolled, once during the course of the study, and finally at study completion. The monitor has the responsibility of reviewing the ongoing study with the investigator(s) to verify adherence to the protocol and to deal with any problems that arise. At all times the sponsor must maintain the confidentiality of the study documents. It is the responsibility of the study monitor to verify the study documents against the subject’s original medical records. The investigator (or his/her deputy) agrees to cooperate with the monitor to ensure that any problems detected in the course of these monitoring visits are resolved. The harmonized SOP ‘Monitoring’ of the trial master file (TMF) (http://www.tmf-ev.de) is utilized for monitoring. The trial monitoring requires a high degree of professional expertise of the monitor. We have a variety of very specific outcome criteria, which are new to the involved trial sites. The focus of monitoring will be on developing, checking and adjusting the trial procedures, and on providing training, mentoring and support to study staff in response to the issues identified. In addition to the on-site monitoring, the following activities are planned: central monitoring of fax data and data management, training of and information on trial staff, and specific support of trial sites (information and download website) and investigators (investigator meetings). Independent audits will also take place in the course of study. The monitoring will be performed for 33% of source data verification, 100% of inclusion and exclusion criteria and 100% of primary endpoint criteria. Pre-study visits prior to the start of the study were carried out for 6 months in advance. A screening visit and six monitor visits per trial site are planned.

### Safety aspects

#### Data Monitoring and Safety Board

The Data Monitoring and Safety Board (DMSB) will be independent of both the investigators and the sponsor. The DSMB will review the blinded safety data, including adverse events reports. The DSMB will be empowered to request the unblinding of the subject’s treatment assignment or to recommend to the study team that this subject should be withdrawn from the study - regardless of the treatment assignment - if an emerging safety signal is suggested. The constitution, governing principles, and mandate of the DSMB are explained in the DSMB charter. The main tasks of the DSMB are to review relevant information about the trial; to ensure adherence to protocol; to advise whether to continue, modify or stop a trial; and to provide the funding organizations with information and advice.

#### Definition of unexpected adverse reactions

An unexpected adverse reaction (UAR) is one that is not listed in the Summary of Product Characteristics or in the Investigator Brochure (SmPC or IB). A UAR includes any event that may be symptomatically and pathophysiologically related to an event listed in the labelling, but differs from the labelled event because of greater severity or specificity.

#### Definition of suspected unexpected serious adverse reactions

Suspected unexpected serious adverse reactions (SUSARs) are serious events that are not listed in the IB or SmPC and that the investigator identifies as related to the investigational product or procedure.

A SUSAR is defined by the following criteria:

 Description and severity of the SAE is not listed in the product labeling (IB or SmPC; GCP-V § 3(9)) and is serious:Life-threatening condition or death.Initial inpatient hospitalization or prolongation of hospitalization required.Significant or persistent or disability or incapacity.Congenital anomaly/birth defect (including that occurring in a fetus).AE (GCP-V § 3(7)).

#### Assessment of severity

For both serious and non-serious AEs, the investigator must determine both the intensity of the event and the relationship of the event to study drug administration. Intensity for each adverse event will be determined by using the Common Terminology Criteria for Adverse Events (CTCAE, version 4.03) of the National Cancer Institute of the USA as a guideline, wherever possible. In those cases where the CTCAE criteria do not apply, the intensity of an adverse event will be defined according to the following criteria:Grade 1 - Mild: causing no limitations of usual activitiesGrade 2 - Moderate: causing some limitations of usual activitiesGrade 3 - Severe: causing inability to carry out usual activities.Grade 4 - Life-threatening: potentially life-threatening or disabling; urgent medical intervention required

In addition, for each AE, the investigator must assess whether the criteria for an SAE are fulfilled.

#### Documentation of adverse events and severe adverse events

Any severe adverse event (SAE) and any adverse event (AE) must be documented, whether it may or may not be considered related to the study drug or the study procedures. The documentation includes the nature of the event, the time point of occurrence, the duration, the severity and the causal relationship of the event.

When recording an AE, the investigator should use the overall diagnosis or syndrome using standard medical terminology, rather than recording individual symptoms, signs or changes in laboratory parameters. Laboratory parameters out of normal range must be assessed by the investigator with regard to the clinical relevance, and in case of clinical relevance, must also be reported as an AE. Any SAE and SUSAR, whether deemed treatment-related or not, must be reported by telephone and fax to the sponsor within 24 hours after the investigator or coordinator has become aware of its occurrence. The sponsor will ensure that all relevant information about SAEs and SUSARs that are fatal or life-threatening is recorded and reported as soon as possible to the national authorities (Federal Institute for Drugs and Medical Devices; Bundesinstitut für Arzneimittel und Medizinprodukte; BfArM) and to the responsible EC.

All other SAEs and SUSARs will be reported to the BfArM and to the EC as soon as possible but within a maximum of 15 days of first knowledge by the sponsor. The sponsor will also inform all investigators.

#### Annual safety reports

Once a year throughout the clinical trial, the sponsor will provide the national authorities BfArM and the EC with a listing of all SAEs and SUSARs that have occurred over this period and a report of the subjects’ safety.

#### Safety profile of hydroxychloroquine

The treatment is generally considered as low risk, and most side effects are not dangerous. The drug has been used successfully for several years in rheumatology and for malaria prophylaxis.

Patients report frequent side effects such as loss of appetite, flatulence, vomiting, diarrhea, headache, nausea, weight loss or unusual tiredness. These symptoms occur mainly during the first weeks of treatment.

Uncommon side effects include dizziness, blurred vision, emotional lability, corneal clouding, hearing impairment, hearing loss, drowsiness, numbness, sleep disturbances, dizziness, tinnitus, confusion, agitation, headache, paresthesia, decreased muscle strength, weakening of the tendon reflexes, changes in sensory perception, ECG changes, conduction disorders, heart disease, and nerve-muscle diseases.

Among the rare side effects are retina problems with visual field defects, impaired color vision, blurred vision, vision loss, changes in skin color, mucous membrane discoloration, bleached hair, gray hair, alopecia, pruritus, photosensitivity, liver problems or failure, beginning of psoriasis, the beginning of porphyria or exacerbation of myasthenia gravis. The very rare side effects include skin rashes, seizures, and methemoglobinemia.

#### Contraindications

Eye diseases with visual field defects, retinopathy, myasthenia gravis, bone marrow suppression, glucose-6-Ph-dehydrogenase deficiency, known allergy to the substance, and breastfeeding are contraindicated. Only under strict indications should HCQ be used when there are concerns about hepatic and renal function, porphyria, psoriasis, seizure disorders, or with concurrent use of monoamine oxidases (MAO) inhibitors in pregnancy. The following measures of therapeutic safety monitoring are provided in this trial:Regular collection and reporting of all adverse events.Medical control of the eyes at baseline and every 6 months.Immediate notification of serious adverse event (SAE), SUSAR, suspected expected serious adverse reaction (SESAR), *etcetera* after becoming aware of the sponsor and follow-up reports within 7 days.Regular meetings of the DSMB and decisions regarding the continuation of the study based on the AE reports.Immediate treatments stop after decision of the investigator.Regular monitoring of laboratory parameters of therapeutic safety.

### Ethics and dissemination

#### Regulatory approval and protocol amendments

Full ethical approval was granted by the independent EC of Berlin (13/029, Landesamt für Gesundheit und Soziales Berlin, LAGeSo) and by the BfArM. Full approval also was given by the Medicines and Healthcare Products Regulatory Agency (EudraCT 2011-001689-16).

The study will be announced to the LAGeSo Berlin. The sponsor and all participating investigators will be designated by their full name and position.

All protocol modifications must be prepared by a representative of the sponsor and initially reviewed and approved by the Trial Core Team (Medical Monitor, Trial Project Manager, Data Safety and Biostatistician) and Monitoring Boards. All protocol modifications must be submitted to the appropriate Independent EC of Berlin. The sponsor informs the BfArM and BMBF about all protocol modifications.

Approval must be awaited before any changes can be implemented, except for changes necessary to eliminate an immediate hazard to trial patients, or when the change(s) involves only logistical or administrative aspects of the trial (for example, change in monitor(s), change of telephone number(s).

#### Insurance

All participating patients are covered for the occurrence of study-related health damage. According to the German Drug Law, the sponsor of the study covers patient insurance.

#### Informed consent

Before the start of the study, the patients will be educated in detail - both verbally and in writing - about the study and the associated risks. Patients will have a decision time of at least 24 hours. It is the responsibility of the investigator, or a person designated by the investigator (if acceptable by local regulations), to obtain written informed consent from each patient participating in this study after adequate explanation of the aim, methods, anticipated benefits, and potential hazards of the study. For patients not qualified or incapable of giving legal consent, written consent must be obtained from the legally acceptable representative. In the case where both the patient and his/her legally acceptable representative are unable to read, an impartial witness should be present during the entire informed consent discussion. After the patient and representative have verbally consented to participation in the trial, the witness’ signature on the form will attest that the information in the consent form was accurately explained and understood. The investigator or designee must also explain that the patients are completely free to refuse to enter the study or to withdraw from it at any time and for any reason. The case report form (CRF) for this study contains a section for documenting informed consent, and this must be completed appropriately. If new safety information results in significant changes in the risk/benefit assessment, the consent form should be reviewed and updated if necessary. All patients (including those already being treated) should be informed of the new information, given a copy of the revised form and give their consent to continue in the study.

#### Study termination

Patients will be informed that they have the right to withdraw from the study at any time for any reason, without prejudice to their medical care. The investigator also has the right to withdraw patients from the study for any of the following reasons (but each patient with one application of HCQ and who is followed to X-ray investigation of the hands at week 52 is included in the trial analyses):Intercurrent diseases.Ophthalmologic changes associated with HCQ.Occurrence of any grade 3 to 4 WHO toxicity or an unacceptable adverse event.A treatment delay or interruption of *>*2 weeks because of toxicity.Patient request.Noncompliance.General or specific changes in the patient’s condition unacceptable for further treatment in the judgment of the investigator.Protocol violations.Medical and ethical discretion of principal investigator.Failure to return for follow-up.

The whole trial may be stopped for the following:Administrative reasons.Incidence of severe adverse events or fatal adverse events. Stopping rules are decided jointly by the data monitoring and safety board.

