### Intervention

Both groups receive standard therapy (NSAID, coxibs) for OA treatment, taken steadily two weeks before enrollment and continued afterwards (Figure 1). If disease activity increases, the dose of NSAID/coxibs can be increased according to the drug recommendation.Group I receives capsules with 200 to 400 mg HCQ as an oral application from day 1 up to the end of week 52. Group II receives capsules as an oral placebo application from day 1 up to the end of week 52. In both groups, a radiological examination is performed at week 52 (Figure 1). Rescue treatment with acetaminophen (maximum of 4 × 500 mg/d) is possible. Ongoing physiotherapy or occupational therapy before screening can be continued unchanged, but must not be commenced after enrollment.

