**Table 2 Tab2:** **Trial timeline, interventions, assessments and visits of OA TREAT**

Primary outcome measures:	
*Clinical endpoint*	Australian-Canadian Osteoarthritis (OA) Index (AUSCAN, German version) dimensions for pain and hand disability as co-primary clinical outcomes at week 52.
*Radiographic co-primary endpoint:*	Radiographic progression from baseline to week 52.
Key secondary endpoints:	
*Clinical outcomes:*	•Assessment and comparison of the inflammatory status using the following parameters: joint pain and joint swelling, night pain, morning stiffness, local erythema/redness, c-reactive protein (CRP) and erythrocyte sedimentation rate (ESR) levels from baseline to week 26,52.
	•Comparison of the increase or decrease of the consumption in the standard medication in the previous 7 days at each visit (non-steroidal anti-inflammatory drugs (NSAIDs), coxibs).
*Patients-reported outcomes*	•Patients global assessment of disease activity, patient’s assessment of stiffness, and physician’s global assessment of disease activity from baseline to week 26,52.
	•Comparison of pain, functioning, disability, quality of life, patient-acceptable symptoms and health with Health Assessment Questionnaire (HAQ), Short Form for the Changes of Quality of Life (SF-36), Short Form for the Assessment and Quantification of Chronic Rheumatic Affections of the Hands (SF-SACRAH), Australian-Canadian Osteoarthritis Index (AUSCAN), *etcetera* from baseline to week 26, 52.
*Assessment of safety*:	
Safety and tolerability of hydroxychloroquine (HCQ) with reports on adverse events (AE) and serious adverse events (SAE) from screening to baseline and week 12, 26, 39, 52, and follow-up of the eyes will be performed by an ophthalmologist at baseline and every 6 months (week 26 and 52).	

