### Methodological aspects

#### Sample size

Our sample size considerations are based on the EULAR recommendations for the planning of RCTs in patients with hand OA [13]. We considered differences in change scores in the AUSCAN scales pain and hand function, which were observed in RCTs comparing NSAIDs (lumiracoxib or ibuprofen) with placebo as clinically relevant differences that also should be detected with a sufficient power in this RCT. For these reasons, we aim to detect an effect size (ES) of 0.4 for pain (SD: 4.3) and of 0.25 for function (SD: 7.3) [13, 29]. An ES of 0.25 is also considered to be relevant for changes in the radiographic scores. Based on these assumptions, a sample size of n=255 per group is sufficient to achieve a power of 95% for the multiple endpoint test (first primary hypothesis) and an 80% power for the second primary endpoint (radiographic progression). The sample size is also sufficient to achieve an at least 80% power when comparing the two AUSCAN subscales pain and hand function separately.

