#### Statistical methods

All patients who received at least one dose of the study medication will be included in the statistical analysis of the efficacy and safety of HCQ (modified intention-to-treat (mITT) population). To control the familywise error rate of 5%, a closed test procedure was applied [30]. In the first step, the first primary hypothesis is tested by means of the multiple endpoint tests according to Läuter and O’Brian [31]. Using this test the outcome in the AUSCAN scales pain and hand function at week 52 is compared between the treatment groups. The multiple endpoint test compares a standardized sum of both outcome measures (AUSCAN pain and function). Since we can assume that the outcome in pain and hand function are correlated, this test is more powerful than a Bonferroni-type test procedure or Hottelling’s T^2^ test [30, 32]. In the case of a significant difference of the first primary hypothesis, the second primary hypothesis (radiographic outcome at week 52) will be tested by means of an analysis of covariance (ANCOVA) based on ranks (nonparametric ANCOVA). Parametric ANCOVA with baseline status as co-variable will be applied to compare secondary outcomes (pain, function, quality of life parameters (SF-36)). Changes in the co-use of NSAIDs and/or analgesics will be compared between both groups. To estimate whether any imbalance in the use might have influenced the outcome in pain and function the suggestions by Dougados *et al*. for comparing different drugs and different dosages will be considered [33]. In the unlikely case that in the verum arm the dosages are more frequently increased by 50% or more (including an increase from 0 mg to half of the full dosage), this finding will be taken into account in the interpretation of the results.

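### The withdrawal rule lets drug- and adherence-related reasons end study participation, and nothing asks these patients to keep the week-52 AUSCAN and X-ray

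*Protocol article*

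**What the plan says.** All references are to the protocol article.

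- **Study termination** gives the investigator a right, not a duty: "The investigator also has the right to withdraw patients from the study for any of the following reasons". The drug-related reasons are HCQ eye changes, grade 3 to 4 toxicity or an unacceptable adverse event, an interruption of more than two weeks for toxicity, and a condition that rules out further treatment. Noncompliance and protocol violations are also listed, as is "Failure to return for follow-up".
- A parenthesis in the same sentence adds that "each patient with one application of HCQ and who is followed to X-ray investigation of the hands at week 52 is included" in the analyses.
- **Statistical methods** defines the modified intention-to-treat population: "All patients who received at least one dose of the study medication will be included in the statistical analysis". The abstract says that analyses follow intention to treat.
- **Intervention** schedules the radiograph: "In both groups, a radiological examination is performed at week 52". The visit schedule in Table 3 shows X-rays at enrolment and week 52 only, and AUSCAN at day 0 and weeks 13, 26, 39 and 52.
- **Contraindications** lists, among the safety measures, an immediate stop of treatment on the investigator's decision.
- **Safety profile of hydroxychloroquine** says of the frequent side effects: "These symptoms occur mainly during the first weeks of treatment".

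**The concern.** Stopping a drug and leaving a trial are different events. An analysis by intention to treat needs outcomes from patients who stopped the drug, and it can use them only if they were collected. The withdrawal list is worded largely in terms of treatment and tolerability, but what it permits is exit from the study.

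The radiographic endpoint is the most exposed. It has one post-baseline reading, so a patient who is not followed to week 52 has no radiographic outcome. AUSCAN has intermediate visits. However, a patient withdrawn for an early adverse event, before the week-13 visit, would have no AUSCAN after day 0 either.

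Toxicity and HCQ eye changes can plausibly be more frequent on HCQ than on placebo, despite blinding. If so, missing outcomes would depend on treatment. An analysis plan can choose how to handle missing data, but it cannot recover an X-ray that was not taken.

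**Working it through.** **1. Does any text require follow-up after withdrawal?**

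| Section | What it settles | Does it oblige week-52 assessment after withdrawal? |
|---|---|---|
| Study termination, list | Who may be withdrawn from the study | No |
| Study termination, parenthesis | That a patient followed to the X-ray is included | No; it describes inclusion and does not mention AUSCAN |
| Contraindications | That treatment can be stopped | No; silent on later visits |
| Intervention and Table 3 | The general schedule | No; silent on withdrawn patients |
| Statistical methods and abstract | Who is analysed | No; not what is collected |

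**2. The plan's own power figures.** Inputs from Sample size: 255 per group; effect size 0.25 for the radiographic score, 0.4 for pain and 0.25 for function; stated power 80% (radiographic) and 95% (combined AUSCAN test). Assumptions: two-sided 5%, and a two-sample t-test in place of the planned rank-based ANCOVA.

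- Radiographic: power at 255 per group is 80.4%, which agrees with the stated 80%.
- Combined test: effect size = (0.4 + 0.25)/√(2 + 2r), where r is the correlation of pain and function. At r = 1 this is 0.65/2 = 0.325, with power 95.6%, which agrees with the stated 95%.

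The planned total of 510 equals 2 × 255.

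**3. Power with X-rays missing.** The loss rates are assumed, equal in both arms and from any cause.

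| Loss | X-rays per group | Radiographic power |
|---|---|---|
| 0% | 255 | 80.4% |
| 5% | 255 × 0.95 = 242.25 | 78.4% |
| 10% | 255 × 0.90 = 229.5 | 76.2% |
| 20% | 255 × 0.80 = 204 | 71.2% |

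The combined AUSCAN test keeps 90.6% at 20% loss with r = 1, and more at lower r. The loss of power therefore matters for the X-ray.

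**4. Possible bias.** Assume that only observed X-rays are analysed and that there is no true effect. If a share w of an arm is lost and its leavers are d SD worse than its completers, the completers look better than the whole arm by w × d. The shift in favour of HCQ is then w(HCQ) × d(HCQ) − w(placebo) × d(placebo). All values below are assumed.

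- 15% lost on HCQ, 5% on placebo, leavers 0.5 SD worse in both arms: 0.15 × 0.5 − 0.05 × 0.5 = 0.05 SD in favour of HCQ. That is 0.05/0.25 = one fifth of the target effect.
- 10% and 5% lost, same gap: 0.10 × 0.5 − 0.05 × 0.5 = 0.025 SD in favour of HCQ.
- 15% and 5% lost, only placebo leavers worse: 0 − 0.05 × 0.5 = −0.025 SD, against HCQ.

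The sign depends on facts that the article does not give.

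**The case against.** **The article is a condensed text.** Follow-up after drug stop is often described in the full protocol, which is not shown, and the clause grants only a right. This limits confidence. But the article does more than omit a follow-up rule: it states a withdrawal rule, and that rule is exit from the study.

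**The wording may be loose.** The parenthesis presupposes that a withdrawn patient can still reach the week-52 X-ray, two of the listed reasons speak of treatment, and Contraindications names a separate treatment stop. The clause may have been meant as withdrawal from treatment. That is a fair reading, and it rules out saying that the plan orders withdrawal or bars later assessment. It still leaves sites without an instruction to obtain the data.

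**The parenthesis.** A reader might infer that placebo patients, or treated patients without a week-52 X-ray, are dropped from the analysis. The documents do not support this. The parenthesis says who is included and excludes nobody, naming only HCQ is probably loose wording for study medication, and Statistical methods includes everyone with at least one dose. This part is mostly editorial.

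**The numbers do not measure this clause.** This stands. Every loss rate and gap is assumed. The thin margin comes from recruiting exactly 2 × 255, and not all loss would come from this rule. The t-test is also only an approximation. If rank analysis costs 4.5% efficiency, the effective size is 255 × 0.955 = 243.5 per group and power is 78.6% with no loss at all. If baseline adjustment instead adds an assumed 10%, power is 84.0% (255 × 1.1 = 280.5), and still 80.1% at 10% loss (229.5 × 1.1 = 252.45).

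**Early withdrawal is inferred.** The article calls most side effects not dangerous and does not say that they lead to study exit. The eye route is probably small: retinal problems are listed as rare, and the scheduled checks after baseline are at weeks 26 and 52, so mainly the week-26 check could cost data.

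**Conclusion.** The point holds as a weakness in the withdrawal rule and is worth fixing, with medium confidence. Applied as written, the rule allows patients to leave the study for drug-related reasons, noncompliance or protocol violations, and nothing in the article asks them to return at week 52. The only post-baseline X-ray may then be missing for reasons that can differ by arm.

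The size and direction of any bias are unknown. A reader might infer that the trial is biased towards HCQ, or that the sample size is wrong. Neither follows: the assumed scenarios shift the result either way, and the stated power figures reproduce. The fall from 80.4% to 78.4% (5% loss) or 76.2% (10% loss) illustrates loss from any cause under a t-test approximation. It is not an estimate of what this clause costs.

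The conclusion rests on the article alone. A follow-up duty in the full protocol would resolve it.

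**What to change.** Amend Study termination as follows.

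- The drug-related reasons end study drug only. The criteria for stopping drug stay unchanged.
- Noncompliance and protocol violations are recorded and do not by themselves end participation.
- Patients off drug in both arms are asked to keep the AUSCAN, safety and week-52 X-ray visits already scheduled.
- Study exit is kept for withdrawal of consent to follow-up, actual loss to follow-up after contact attempts, and the principal investigator's medical or ethical judgement that further assessments would harm the patient.
- The parenthesis is aligned with Statistical methods: all patients with at least one dose of HCQ or placebo.

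**Cost.** Regulatory approval and protocol amendments requires internal review, ethics committee approval before use, and notice to BfArM and BMBF. Sites need a letter and must stay in contact with patients who are off drug. No new procedure is added. Trial status reports recruitment and follow-up in progress, so later week-52 data can still be secured, but data from patients already withdrawn may not be recoverable.
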